### Study participants and measurements

All participants will be selected from among patients visiting the emergency rooms of two general hospitals in Korea (Seoul National University Bundang Hospital, Seoul National University Boramae Medical Center). Patients aged over 18 years who have moderately severe to severe symptoms and glucose-corrected sNa [25] ≤125 mmol/L on the first blood test will be screened for study participation. Moderate symptoms include nausea, headache, drowsiness, general weakness, and malaise [1, 26, 27]. Severe symptoms include vomiting, stupor, seizure, and coma (Glasgow Coma Scale (GCS)).

The following assessments will be performed during the initial emergency room encounter: (1) completion of questionnaire on medical and drug history including the use of antihypertensive medication, diuretics, nonsteroidal anti-inflammatory drugs, selective serotonin reuptake inhibitors, antiepileptic drugs, steroids, and synthyroid, (2) physical examination of all body systems, (3) measurement of height and weight, (4) blood pressure and pulse rate measurement, and (5) assessment of psychological status. Participants, who meet all of the inclusion criteria, do not require exclusion on the basis of the exclusion criteria, and provide written informed consent will be eligible for this study (Table 1).

**Table 1 Tab1:** Inclusion and exclusion criteria

Inclusion criteria	Exclusion criteria
18 years and older	Pseudo-hyponatremia (serum osmolality >275 mOsm/kg)
	Primary polydipsia (urine osmolality ≤100 mOsm/kg)
	Glucose-corrected serum sodium >125 mmol/L
	Initial arterial hypotension (SBP <90 mmHg and MAP <70 mmHg)
Glucose-corrected serum sodium ≤125 mmol/L	Anuria or urinary outlet obstruction
	Decompensated LC (LC with ascites or diuretics use or history of hepatic encephalopathy and varices)
	Bilirubin >2 mg/dL, transaminase levels >2.5 times the upper limit of normal)
Symptomatic patients	Uncontrolled diabetes mellitus (HbA1C >9%)
Moderately severe:	Women who are pregnant or breastfeeding
nausea without vomiting, drowsiness, headache, general weakness, malaise	Within the 3 months prior to randomization, history of cardiac surgery excluding PCA, acute myocardial infarction, sustained ventricular tachycardia, ventricular fibrillation, acute coronary syndrome, cerebrovascular trauma, and increased intracranial pressure
Severe:	
vomiting, stupor, seizures, coma (GCS ≤8)	

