### Physician’s practical treatment guidelines according to the sNa level

The principal purpose of this study will be to compare the rapid intermittent correction group to the slow continuous correction group [29]. According to a review of the medical literature on the treatment of hyponatremia, treatment with hypertonic (3%) saline is recommended in cases of severe symptomatic hyponatremia [1, 15, 16]. Therefore, the rate of infusion of 3% saline will be stratified based on the symptom severity in each group. After randomization, the participants will undergo either rapid intermittent correction or slow continuous correction of hyponatremia for 48 h. Treatment in the intermittent bolus group will comply with European guidelines published in 2014, and the slow continuous infusion will be guided by widely accepted methods [1, 13–16]. The treatment goals are to raise the sNa level by 5–9 mmol/L from the initial sNa and to achieve symptom relief within the first 24 h, and to raise the sNa level by 10–17 mmol/L from the initial sNa or ≤130 mmol/L, and to achieve symptom relief during the 48 h [10–12]. We will also check for overcorrection at every sample time point and conduct relowering treatment. Relowering treatment is performed as below if the achieved sNa level is ≥10 mmol/L at any sample time point within the first 24 h or the achieved sNa level is ≥18 mmol/L at any sample time point within 48 h [1, 13–16]. The treatment goal, relowering treatment strategy, and cause-specific treatment of hyponatremia will be applied to each group equally.

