### From 24 to 48 hours

In both moderately severe and severe cases of hyponatremia, repeated infusion of 2 mL/kg 3% hypertonic saline over 20 min at every sample time point (at 30, 36, 42, and 48 h) is recommended until the sNa level increases to 10–17 mmol/L from the initial sNa or until the sNa reaches 130 mmol/L, and until the symptoms improve.

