### From 24 to 48 hours

The infusion protocol will be modified as below according to the sNa levels at every sample time point (at 30, 36, 42, and 48 h). If the Na level increases to 10–17 mmol/L above the initial sNa level or sNa reaches 130 mmol/L, and symptom relief is observed, the 3% hypertonic saline infusion should be discontinued regardless of changes in the sNa level during the previous 6 h. If the Na level increase is less than 1.5 mmol/6 h, it is recommended to add 3% hypertonic saline infusion at a rate of 0.25 mL/kg/h to the previous infusion rate or to restart the infusion at a rate of 0.25 mL/kg/h if it was previously discontinued. If sNa levels increase at a rate of over 1.5 mmol/6 h, the 3% saline infusion rate should be maintained.

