### Outcome measures

The primary outcome is the incidence of overcorrection, a surrogate marker of ODS, at any given period, defined as follows: increase in sNa level by >12 mmol/L within the first 24 h or increase in sNa level by >18 mmol/L within 48 h. The secondary outcomes will include efficacy and safety; changes in symptoms between pretreatment and 24 and 48 h after treatment with 3% hypertonic saline; time from treatment initiation to an increase in sNa ≥5 mmol/L; time from treatment initiation to the achievement of a sNa >130 mmol/L; incidence of target correction rate, defined as an achieved sNa <10 mmol/L within 24 h and a sNa <18 mmol/L within 48 h; length of hospital stay; incidence of additional treatment; incidence of ODS confirmed by the *International Classification of Disease, 10th Revision (ICD-10)* code or magnetic resonance imaging (MRI); incidence of relowering treatment; and change in GCS score between pretreatment and 24 and 48 h after 3% hypertonic saline treatment.

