### Clinical and laboratory evaluations

The physical examination, laboratory evaluations, and medication reviews will be conducted before treatment; the laboratory evaluations will include a complete blood count, serum electrolytes, blood urea nitrogen, creatinine, calcium, phosphorous, protein, albumin, and glucose; a liver function test; a thyroid function test (TFT); rapid adrenocorticotropic hormone (ACTH) test (basal cortisol, ACTH, cortisol at 30 min and 60 min), serum osmolality; urinalysis, urine electrolytes, urine osmolality. sNa levels will be measured every 6 h for 2 days [30]. The GCS score will be assessed before treatment and at 24 and 48 h of treatment. All types and volumes of administered fluid during 48 h will be monitored.

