### Statistical analyses

Statistical analyses will be performed on both per-protocol (PP) and intention-to treat (ITT) bases. For the PP analysis, all participants who completed the study will be included to evaluate the primary and secondary outcomes. For the ITT analysis, all participants who were enrolled and randomized to one of the two groups will be included. The baseline characteristics and laboratory data will be presented as means and standard deviations for continuous variables and as frequencies and percentages for categorical variables.

The incidence of overcorrection, ODS, relowering treatment, and target correction rate (achieved sNa <10 mmol/L within the first 24 h and sNa <18 mmol/L within 48 h) will be compared between the two groups using a *χ*
^*2*^ test and Fisher’s exact test. In interim analysis, if the *P* value < 0.003 then we would stop the study early for significance of outcome. If not, we would recruit another half of subjects. The differences in changes in symptoms and GCS scores between pretreatment and 24 and 48 h, time to reach target sNa, time to achieved sNa ≥5 mmol/L for the first time, and length of hospital stay will be analyzed using Student’s *t* test or the Mann-Whitney *U* test. A value of *P* < 0.05 will be considered statistically significant. All analyses will be performed using SPSS Statistics software V21.0 (IBM Corporation, Armonk, NY, USA).

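### Time-to-sodium outcomes are assigned a t test or Mann-Whitney test with no rule for patients who do not reach the level by 48 h; for sNa >130 mmol/L, not reaching it is built into the treatment rules

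*Protocol article*

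**What the plan says.** Outcome measures lists two time outcomes among the secondary outcomes: "time from treatment initiation to an increase in sNa ≥5 mmol/L" and "time from treatment initiation to the achievement of a sNa >130 mmol/L". Statistical analyses names the test for them: "time to reach target sNa, time to achieved sNa ≥5 mmol/L for the first time, and length of hospital stay will be analyzed using" either a t test or a Mann-Whitney test. The first of the times in that sentence is to a target sodium, which the sentence does not define. The same section defines the intention-to-treat set as everyone randomized.

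Observation of sodium is limited: "sNa levels will be measured every 6 h for 2 days" (Clinical and laboratory evaluations).

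The treatment rules bear on who can exceed 130:
- Entry (Table 1): "Glucose-corrected serum sodium ≤125 mmol/L", with no lower limit.
- The 48 h goal (Physician's practical treatment guidelines): "to raise the sNa level by 10–17 mmol/L from the initial sNa or ≤130 mmol/L".
- Bolus group, second day: infusions are repeated "until the sNa level increases to 10–17 mmol/L from the initial sNa or until the sNa reaches 130 mmol/L", and until symptoms improve.
- Continuous group, second day: "If the Na level increases to 10–17 mmol/L above the initial sNa level or sNa reaches 130 mmol/L", with symptom relief, the infusion is discontinued.
- Safety issues: relowering is triggered at 18 mmol/L or more within 48 h, read here as a rise from the initial value.

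**The concern.** A t test or rank test needs a value for every patient. A patient still below the level at 48 h has no observed time, only the knowledge that the time exceeds 48 h. The article does not say what becomes of such a patient. If the test is run on the recorded times, as the named methods do by default, non-reachers leave the comparison. What remains is a comparison of patients selected by an event after randomization. An arm that brings fewer patients to the level can then look equal, or even faster.

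For sNa >130 there is a second difficulty. At the lowest baselines a recorded time exists only if the patient had the harm that the primary outcome counts. The sample size section expects overcorrection to differ between arms (5% vs 20%), so membership of the reachers' group may itself depend on treatment. A short time to >130, read alone, could credit overcorrection as efficacy.

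**Working it through.** **1. The plan's own figure.** The article gives no figure for the time outcomes, but its sample size supplies the n for the check below. With 20% vs 5%, two-sided 5% and 80% power, the mean proportion is 0.125:

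n = [1.96·√(2·0.125·0.875) + 0.8416·√(0.20·0.80 + 0.05·0.95)]² / 0.15² = 75.12 per group.

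Allowing for 15% dropout, 75.12/0.85 = 88.4, rounded up to 89. This reproduces the stated 89 per group. About 76 evaluable patients per arm is used in step 4.

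**2. Who can exceed 130?** In whole mmol/L, exceeding 130 means 131 or more, so the rise needed is 131 minus baseline.

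| Baseline sNa | Rise needed for 131 | Position under the rules |
|---|---|---|
| ≤112 | ≥19 | above 18, so primary-outcome overcorrection if within 48 h |
| 113 | 18 | above the 10–17 goal, at the relowering trigger |
| 114–120 | 11–17 | within the 48 h goal, but with symptom relief saline may stop at +10, i.e. at 124–130 |
| 121–125 | 6–10 | saline may stop at 130 |

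The first row does not depend on rounding: 130 − 112 = 18, so any value above 130 is a rise above 18. At every eligible baseline, a patient whose symptoms improve can be treated exactly to protocol and never exceed 130. From 114 upward a patient may also exceed 130 within the rules.

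**3. The rise of at least 5 mmol/L.** This is the lower end of the 24 h goal of 5–9, and both arms repeat or step up saline towards it. Few non-reachers would be expected, but any that occur have no assigned value.

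**4. What a reachers-only test can do.** The reach rates below are assumptions, because the documents give none. Settings: 76 per arm, exponential times, sampling at 1, 6, 12, 18, 24, 30, 36, 42 and 48 h, 1,000 runs, two-sided 5%, no stratification. Monte Carlo error is about 1.5 percentage points.

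| Reach by 48 h | t test, reachers only | Log-rank, censored at 48 h | Mann-Whitney, non-reachers last |
|---|---|---|---|
| 20% vs 40% | 5% | 77% | 77% |
| 30% vs 50% | 8% | 74% | 73% |
| 40% vs 60% | 9% | 69% | 68% |
| 50% vs 70% | 11% | 78% | 75% |
| 90% vs 97% | 36% | 69% | 58% |

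The direction can also reverse. Suppose 30% vs 60% reach the level, and the arm with fewer reachers is 6 h faster among those who do (normal times, SD 10 h). The reachers-only mean then favours that arm by 5.7 h, and the t test is significant in 61% of runs.

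**The case against.** The best defence is that no sentence says non-reachers are dropped. The intention-to-treat set covers everyone randomized, and Mann-Whitney, one of the two named tests, works well if non-reachers are ranked last. The table bears this out: worst-rank Mann-Whitney is close to log-rank except when nearly everyone reaches the level. A condensed article may also leave such a rule to an analysis plan. The first part stands, and exclusion is treated here only as the default consequence. The last part stands only partly. The article does fix the test, one of its two options cannot use a patient without a time, and the other needs a rule that is not given.

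Three stronger readings are tempting, and the documents do not support them:
- A reader might infer that many patients will fail to reach both levels. No baseline sodium distribution is given, so the number cannot be stated for >130. For the rise of at least 5 mmol/L the dosing rules point the other way.
- A reader might infer that saline always stops at a rise of 10–17 or at 130. Both arms also require symptoms to improve, and cause-specific treatment runs alongside, so some patients will pass 130 within protocol.
- A reader might infer that the trial's efficacy conclusion rests on these times. They are unranked secondary outcomes. Changes in symptoms and in Glasgow Coma Scale score do not depend on reaching a sodium level.

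Finally, the target sodium in Statistical analyses may not mean >130. If it means the treatment goal, the structural argument does not attach to that test, and time to >130 then has no named analysis. Either way the two sections need reconciling.

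**Conclusion.** The concern holds as a defect in a stated method for secondary outcomes, and should be fixed. The named tests do not suit times observed only to 48 h unless non-reachers are given a rule, and none is stated. For sNa >130 this follows from the treatment rules at every eligible baseline. For the rise of at least 5 mmol/L it is a smaller gap.

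The size cannot be read from the documents. It rests on assumed reach rates and on the assumption that the test would be run on observed times. On that basis a 20-point difference in reach would be detected 5–11% of the time by a reachers-only t test and 69–78% of the time by log-rank. The reversal example shows what is possible and does not predict a result. The primary outcome, its test and the 89 per group are untouched.

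**What to change.** Replace the test for the two time outcomes with the following:

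- Analyse all randomized patients with Kaplan-Meier curves and a log-rank test stratified by symptom severity, the randomization stratum. Censor non-reachers at their last sodium, at most 48 h. Alternatively, pre-specify Mann-Whitney with non-reachers ranked last, and say how patients who leave before 48 h are ranked.
- Report, by arm, the proportion reaching each level by 24 h and by 48 h.
- Define the target sodium once, so that Outcome measures and Statistical analyses name the same event.
- Report time to >130 beside the overcorrection results, and do not read a short time alone as efficacy.

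Overcorrection need not be made a competing event. From a low baseline both events can fall on the same sample, and doing so would change what the outcome measures.

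The cost is a revised paragraph and slightly more analysis work. Treatment, data collection and sample size do not change.

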### Data and safety monitoring

The paper data collection sheets and signed informed consents will be stored in a locked cabinet, and the electronic data base will be stored on password-protected secure severs. Any unanticipated adverse events that occur during the study will be reported to the Institutional Review Board in accordance with the procedures of Seoul National University Bundang Hospital, Korea. For any revised study procedure, the modification will be submitted to the Seoul National University Bundang Hospital Institutional Review Board for approval and to ClinicalTrials.gov. The data will be kept confidential with only limited access to research investigators.

## Discussion

Recently published guidelines recommended the prompt infusion of small, fixed boluses of hypertonic saline in patients with symptomatic hyponatremia [1, 15, 16]. This regimen leads to abrupt incremental increases in sNa levels and improvement of hyponatremia-related symptoms [1, 15, 16]. However, safety issues regarding rapid correction with hypertonic saline have not been evaluated. No large-scale randomized controlled trials to evaluate and compare the efficacy and safety of rapid and slow correction with hypertonic saline have been performed. This is the first clinical trial to provide physicians with quality evidence regarding treatment with hypertonic saline in patients with moderately severe or severe hyponatremia. In addition, a protocolized approach, such as that of this study, may be extended to the management of other electrolyte disorders.

In the development of this protocol, we complied with recent guidelines, particularly in determining the target sNa levels, in the method of infusion of 3% hypertonic saline for the rapid correction group, and in the classification of symptoms of hyponatremia [1, 15, 16]. Recently published guidelines recommended prompt intravenous infusion of 100–150 mL 3% hypertonic saline over 10–20 min, repeated once or twice as needed, in the initial treatment of severe hyponatremia [1, 15, 16]. We adopted a weight-based approach (2 mL/kg) rather than the fixed 100–150-mL infusion volumes of 3% hypertonic saline in this study because Koreans tend to have smaller physiques than Westerners. Recent guidelines recommended discontinuing the infusion of hypertonic saline in cases of improvement of symptoms after a 5-mmol/L increase in sNa and initiating a diagnosis-specific treatment [1]. Our planned approach to decreases or no change in sNa levels during the diagnosis of hyponatremia and the initiation of cause specific treatment was to repeat a bolus infusion every 6 h until sNa incrementally increases to the target level and symptom relief were observed. This approach is different from the protocols recommended by recent guidelines [1]. In the slow continuous correction group, we adopted a 3% hypertonic saline infusion rate of 0.5–1 mL/kg/h, a widely known treatment approach [10, 11], according to symptom severity. Recent guidelines define indicative symptoms of cerebral edema as severe or moderate symptoms that can be attributed to hyponatremia [1]. In our study, general weakness and malaise, usually considered nonspecific, were included as moderate symptoms of hyponatremia. Our rationale for including these as symptoms of hyponatremia are as follows: first, patients start complaining of nausea and malaise as sNa concentration falls acutely below 125 mmol/L [27]. Malaise is thus a result of hyponatremia and is as significant as nausea. Second, patients with symptomatic hyponatremia, including weakness and malaise, should be treated with hypertonic saline [26]. As this clinical trial aims to compare the efficacy and safety of rapid versus slow hypertonic saline administration in the correction of hyponatremia, we included general weakness and malaise as hyponatremia-defining symptoms.

A previous study reported that the overcorrection rate was 10–16% in slow continuous correction of hyponatremia [10]. According to unpublished retrospective data in our hospital, overcorrection in the slow continuous correction group occurred in approximately 32% out of 129 hyponatremic patients during a recent 1-year period. Although Moritz et al. reported that there is little or no risk of inadvertent overcorrection [20], data on the rapid intermittent correction regimen were unavailable. We therefore expect that the overcorrection rate will be 5% in patients treated with rapid intermittent correction, and the overcorrection rate in slow continuous correction could be as high as 20%. For this reason, we will plan to perform an interim analysis, which will be conducted after a number of patients equal to half the estimated total sample size have been enrolled. No previous studies addressing differences in efficacy between rapid intermittent correction groups and slow continuous correction groups in each stratification group have been reported. In the interim analysis, we will also examine the ratio of stratification (moderately severe versus severe) for each experimental therapy group and analyze the efficacy of rapid intermittent correction compared to slow continuous correction for each level of stratification. After the interim analysis, the total study population of 178 patients will be adjusted to the ratio of stratification in the experimental therapy groups. In the interim analysis, if the *P* value < 0.003 then we will stop the study early for significance of outcome. If not, we will recruit another half of subjects.

We will also include the participants with chronic hyponatremia. It is well-known that using a threshold of 48 h is frequently applied to distinguish “acute” from “chronic” hyponatremia [1]. Because not all patients have sNa measured within 48 h prior to visiting the emergency room. Therefore, it is practically impossible to exclude the patients with chronic hyponatremia based on these definitions. Second, the most important factor in determining treatment of hyponatremia is the presence of symptoms, irrespective of biochemical degree or timing (acute versus chronic) of hyponatremia [1]. We will enroll the patients with moderately severe to severe symptoms who need to be treated. In other words, even if the patients belong to the chronic hyponatremia group, the patients with symptomatic hyponatremia need to be treated. Therefore, we thought that including the patients with chronic hyponatremia is reasonable and inevitable.

We will use the overcorrection rate as a primary outcome. ODS is a serious complication, which should be prevented for patient safety, and it is one of the critical outcomes in the management of hyponatremia, but it is difficult to diagnose and very uncommon [1, 31]. Several studies have reported that the rate of overcorrection is strongly correlated with ODS, and is highly sensitive for predicting ODS. In terms of safety issues, the overcorrection rate might be a good laboratory outcome in our trial [1, 15, 32, 33].

This trial may have some limitations. We will enroll patients who visit the emergency room in general hospitals; therefore, patients with hospital-acquired hyponatremia will be excluded. Second, various situations may affect protocol violations, considering that on-duty physicians and nurses may work in shifts. For this, reason we made both protocols as simple as possible.

In summary, the SALSA study is the first prospective, multicenter, randomized, open-label, controlled clinical trial to evaluate the clinical usefulness of rapid intermittent correction management in patients with moderately severe or severe hyponatremia. The aim of this study is to evaluate the efficacy and safety of rapid bolus correction compared with slow continuous correction of hyponatremia.

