### Study design

This study is a prospective, investigator-initiated, multicenter, open-label, randomized controlled study with two experimental therapy groups. We have followed the Standard Protocol Items: Recommendations for Interventional Trials (SPIRIT) 2013 Statement which defines standard protocol items for clinical trials [24] (see Additional file 1). The study algorithm is depicted in Fig. 1 and the SPIRIT and study schedule are given in Figs. 2 and 3. After enrollment, clinical follow-up will be performed 2 days after treatment with 3% hypertonic saline.

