### Randomization

A research coordinator will perform the randomization. A list of random numbers will be generated by an independent statistician. Eligible participants will be randomly assigned 1:1 to either the slow continuous correction group or the rapid intermittent correction group in accordance with the predefined randomization list with a block size of 2. Randomization will be stratified based on the symptom severity related to hyponatremia (moderately severe or severe).

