### Safety issues

All adverse events related to overcorrection will be recorded and followed up during the study period or until resolution during treatment with 3% hypertonic saline. Any serious adverse events will be reported to investigators and the Ethics Committee. We will check for overcorrection at every sample time point and conduct relowering treatment as needed. Relowering treatment is performed as follows if the achieved sNa level is ≥10 mmol/L at any sample time point within the first 24 h or if the achieved sNa level is ≥18 mmol/L at any sample time point within 48 h: discontinuing ongoing active treatment; initiating infusion of 10 mL/kg of 5% dextrose over 1 h; and/or adding desmopressin 2 mcg [1].

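### The half-way look includes an efficacy comparison of the arms within each severity stratum that no stated decision needs, and as worded the trial team would see it before recruiting the second half of an open-label trial

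*Protocol article*

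**What the plan says.** Study design describes a "prospective, investigator-initiated, multicenter, open-label, randomized controlled study with two experimental therapy groups".

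Sample size calculation plans one interim analysis of the primary outcome, with O'Brien-Fleming-type alpha spending. Statistical analyses sets the early-stopping limit at P < 0.003.

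The Discussion adds two further tasks at the interim. One is descriptive: "In the interim analysis, we will also examine the ratio of stratification (moderately severe versus severe) for each experimental therapy group". The other compares outcomes between arms: the authors will "analyze the efficacy of rapid intermittent correction compared to slow continuous correction for each level of stratification". After the interim, "the total study population of 178 patients will be adjusted to the ratio of stratification in the experimental therapy groups". On missing the stopping limit it says: "If not, we will recruit another half of subjects".

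The article mentions an independent statistician once, under Randomization: "A list of random numbers will be generated by an independent statistician". On data access, Data and safety monitoring says: "The data will be kept confidential with only limited access to research investigators".

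**The concern.** The Discussion uses one grammatical subject throughout: those who compare the arms by stratum also decide on stopping and recruit the remaining patients. Treatment is not masked. If people who enrol or treat patients learn mid-trial which arm is overcorrecting more, overall or in one stratum, their care and enrolment in the second half can change by arm.

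The primary outcome is a laboratory value, which protects its measurement. Whether sodium rises by more than 12 mmol/L in 24 h or more than 18 mmol/L in 48 h still depends partly on care. A change in care that differs by arm creates or hides a difference that the regimens themselves did not cause. Alpha spending controls for testing twice; it does not control for this.

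**Working it through.** **1. The plan's own figures reproduce.**
- Inputs from Sample size calculation: 20% vs 5%, two-sided 5%, 80% power, 15% dropout.
- n = [1.96·√(2·0.125·0.875) + 0.842·√(0.20·0.80 + 0.05·0.95)]² / 0.15² = 75.1 per arm. Then 75.1/0.85 = 88.4, which rounds up to the stated 89.
- O'Brien-Fleming-type spending at half the information, as two one-sided 0.025 functions: 4·[1 − Φ(Φ⁻¹(0.9875)/√0.5)] = 0.00305, matching the stated 0.003.

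The point below is about conduct, not about a wrong number.

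**2. Which interim results feed a stated decision?**

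| Interim item | Decision it feeds | Needs outcomes by arm? |
|---|---|---|
| Primary outcome, P < 0.003 | Stop or continue | Yes |
| Ratio of moderately severe to severe | Adjustment of the 178 | No |
| Efficacy by arm within each stratum | None stated | Yes |

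The third row can be dropped from the interim without losing any decision in the plan. It would also be imprecise. With 89/2 = 44.5 per arm and an assumed stratum share of 25–75% (the article gives none), a stratum has about 11 to 33 per arm. At 20% vs 5%, the 95% half-width is 1.96·√[(0.16 + 0.0475)/m], about 27 points at m = 11.1 and 15 points at m = 33.4. The planned difference is 15 points.

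**3. How likely is continuation after the look?** At 20% vs 5%, the chance of crossing P < 0.003 is about 12% with 38 per arm (half of the evaluable patients) and 15% with 44 per arm (half of those randomized). Even if the planned effect is true, the trial continues in about 85–88% of cases.

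**4. Where does care leave discretion?**
- Most saline steps in the two treatment sections are worded as recommended, and stopping also requires judged symptom relief.
- Safety issues says: "We will check for overcorrection at every sample time point and conduct relowering treatment as needed". The next sentence gives numeric triggers (≥10 within 24 h, ≥18 within 48 h) but an and/or choice for adding desmopressin. The 24-h trigger lies below the >12 of the primary outcome, so relowering can act before an event occurs.

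**5. Illustration of size; the shifts are assumptions.** Simulation of 400,000 trials: 12.5% in both arms (midway between 5% and 20%), 38 + 37 = 75 per arm (89·0.85 = 75.65), rejecting at interim P < 0.003 or final P < 0.049. In the second half one arm's rate rises by d points and the other's falls by d, so the gap is 2d.

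| d (points) | Second-half rates | Type I error, direction fixed in advance | Type I error, direction follows interim trend |
|---|---|---|---|
| 0 | 12.5% vs 12.5% | 5.0% | about 5% |
| 1 | 13.5% vs 11.5% | 5.4% | about 7% |
| 2 | 14.5% vs 10.5% | 6.5% | about 11% |
| 3 | 15.5% vs 9.5% | 8.4% | about 15% |
| 4 | 16.5% vs 8.5% | 11.2% | about 20% |

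The last column models knowledge of the interim result. The fixed-direction column describes general drift in an open-label trial.

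The bias can also run the other way. With 89 per arm, a single final test at 0.05 and true rates of 5% vs 20%, a second-half control rate lowered by 5 or 10 points cuts power from 89% to 78% or 62%.

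**The case against.** The strongest objection is that the article never says who runs the interim or who receives its results. Authors write in the first person plural about everything, including work done by others, and a condensed article may leave access rules to the full protocol. This stands. A reader might infer that the investigators themselves will analyse and see the comparison, or that the lack of a named monitoring committee is a fault. The first is only the plain reading of the wording, and the second cannot be held against an article.

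A reader might also take the data-access sentence in Data and safety monitoring as handing interim results to the investigators. It does not say so: it sits beside locked cabinets and password-protected servers, and it limits access.

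Nor do the documents show that those who would see the interim results also judge symptom relief. The Discussion refers to on-duty physicians and nurses working in shifts and says both protocols were kept simple for that reason. The relowering triggers are numeric, and the treatment guidelines section applies the treatment goal and the relowering strategy equally to both groups. Discretion is therefore partial.

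Finally, open-label staff already see each patient's arm and sodium course, so some differential care is possible without any interim. That is true, and restricting interim results would not remove it. It would remove the added effect of knowing the accumulated difference.

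None of this gives the by-stratum efficacy comparison a purpose at half-way.

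**Conclusion.** The point holds in a limited form. The Discussion commits an open-label trial to a mid-trial comparison of the arms by stratum that serves no stated decision and, as worded, reaches the team that goes on recruiting. This is an avoidable risk of bias, not a demonstrated one.

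Its size cannot be derived from the documents. The 6.5–11% and 11–20% ranges rest on assumed shifts of 2 to 4 points in each arm (gaps of 4 to 8 points), 12.5% in both arms and 75 per arm. They should not be read as this trial's type I error. The conclusion also depends on reading the first person plural as the trial team; if a fuller document already restricts interim results, only the wording needs correcting. The change is worth making because it costs little, but confidence that harm would follow is low.

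**What to change.** Replace the interim text in the Discussion, and align Statistical analyses with it, as follows:

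- The interim consists only of the primary-outcome test at P < 0.003.
- It is run by a statistician not involved in enrolment or treatment, for example the independent statistician who makes the randomization list, if available. That person returns only stop or continue.
- Any adjustment of the 178 uses the ratio of moderately severe to severe patients pooled over the arms, without outcome data.
- The by-stratum efficacy comparison moves to the final analysis. No result by arm or by stratum goes to anyone who enrols or treats patients before the last patient completes 48 h.

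If a fuller protocol already contains such a restriction, one sentence stating it would do in place of the second item.

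Cost: one paragraph, plus some statistician time, since the article gives the independent statistician only the list to prepare. The team waits for the stratum results. No treatment rule, sample size or stopping limit changes.
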